## Abstract

**Background:**

With the existence of various frozen embryo transfer (FET) methods currently used in the field of assisted reproductive technologies, the debate surrounding which of these is superior remains. All FET protocols aim to prime the endometrium and time embryo transfer during the window of implantation. Current methods include the true natural cycle FET (tNFET), modified natural cycle FET, artificial cycle FET, and ovulation induction. Each of these harbors, distinct advantages and disadvantages, namely, surrounding the timing of transfer and flexibility conferred through this process. More recently, a newer approach has been used whereby the need to monitor or trigger ovulation is circumvented, with luteal phase support commenced once a certain follicle diameter and endometrial thickness criteria are met but before ovulation. However, the research into this protocol has certain important limitations that our study seeks to address.

**Objective:**

This study aims to assess the feasibility of a progesterone-modified natural cycle protocol for FET. The primary outcome will be the presence of a corpus luteum on ultrasound scans on the day of embryo transfer. The secondary outcomes will include the number of clinic visits required per patient undergoing the protocol, biochemical pregnancy rate, and clinical pregnancy rate.

**Methods:**

We will conduct a prospective cohort study, recruiting 20 women undertaking FET at the Public Fertility Care of The Royal Women’s Hospital in Melbourne, Australia. These women will be matched to a control group who have undergone the tNFET protocol within the preceding 12 months of the study start date.

**Results:**

This project received ethics approval on July 17, 2024, with commencement of the study in September 2024, aiming for a duration of completion of 9 months. The completion of the follow-up and submission of the study for publication are anticipated for September 2025.

**Conclusions:**

After this preliminary study, the aim would be to progress to a noninferiority randomized controlled trial to compare the progesterone-modified natural cycle protocol for FET to the tNFET.

**International Registered Report Identifier (IRRID):**

PRR1-10.2196/66579

## Introduction

Frozen embryo transfer (FET) has been increasingly used over recent decades in Europe [1,2] and Australia [2]. With advancements in cryopreservation techniques and increasing use of FET, debate still exists around the optimal method of endometrial preparation to achieve the best possible pregnancy rates and improve various maternal and neonatal outcomes. The most widely used protocols for endometrial preparation include the natural cycle FET (NFET), artificial cycle FET (AFET), and ovulation induction methods [3], with the latter two protocols usually reserved for anovulatory women. While the true NFET (tNFET) relies on monitoring for a surge of endogenous luteinizing hormone (LH) and rise in progesterone (P4) as markers of ovulation to time P4 supplementation start and embryo transfer, the AFET protocol involves exogenous hormone (estrogen, followed by P4) administration to mimic the natural cycle and prime the endometrium. Furthermore, while the AFET confers greater flexibility in terms of timing FET precisely, there is evidence to suggest lower overall implantation rates and higher miscarriage rates from this technique [4]. The literature also suggests there may be a higher rate of obstetric complications for both mother and fetus, including pre-eclampsia [5] and fetal macrosomia [6]. Therefore, the advantage of tNFET centers on avoiding excessive exogenous hormone administration and the resulting adverse events (AEs) linked to AFET. However, the inflexibility conferred by the tNFET in terms of the need to closely monitor endometrial thickness, follicle size, and hormone levels may require multiple blood tests and 7-day in-vitro fertilization clinic availability. Further, the ovulation induction protocol involves the expense and invasiveness of using medication without removing the need for a 7-day service or the need for blood tests. Therefore, a protocol that achieves ovulation and gives a degree of flexibility to the timing of embryo transfer would be highly appealing to both patients and in-vitro fertilization clinics.

To address these challenges, some clinics use the modified NFET (mNFET) protocol where exogenous human chorionic gonadotropin (hCG) is administered to trigger ovulation when a dominant follicle of typically 17 mm or more is detected, thereby conferring some flexibility in scheduling FET while still relying on the woman’s natural cycle [7]. Retrospective cohort studies have shown favorable outcomes in both the tNFET and mNFET as compared to the AFET [8]. Notably, two recent randomized controlled trials (RCTs) showed similar rates of pregnancy in the mNFET as compared to the tNFET, with higher implantation rates in the mNFET cohort [7,9]. However, at least one study has reported better outcomes with tNFET [10], and the most recent Cochrane systematic review on cycle regimens of FET did not compare tNFET and mNFET [3].

To further explore the potential flexibility conferred by the mNFET method while mitigating the lack of flexibility in scheduling the transfer, a prospective case series proof-of-concept study by Weiss et al [11] has trialed a novel approach whereby timing the FET to the endogenous LH surge is circumvented. Instead, P4 luteal phase support (LPS) via vaginal pessary is commenced once a mature follicle of >12 mm is identified in ultrasound scans and the lining of the endometrium is sufficiently thick at >7 mm, with FET scheduled 2-5 days from this point, depending on the stage of the embryo at the time of cryopreservation. It appears that this P4-modified natural protocol for FET (P4mNFET) provides a simultaneous advantage of both retaining a natural cycle, with authors suggesting ovulation took place regardless, as well as conferring greater flexibility for the scheduling of embryo transfer without compromising clinical pregnancy rates. It should be noted that the authors report a degree of variation in the timing of P4 initiation in relation to the last ultrasound scan without any further blood tests. Importantly, no AEs were reported from this study of 42 participants. A more recent retrospective cohort study comparing this method to AFET demonstrated comparable outcomes in terms of clinical pregnancy, miscarriage, and live birth rates between the methods [12]. A further single-center retrospective cohort study reported similar results when comparing outcomes from patients undergoing FET cycles within the natural and artificial protocols, as compared to a P4mNFET protocol [13]. Taken together, P4mNFET may confer greater flexibility to clinicians and patients in timing FET, negating the requirement to await ovulation, with comparable outcomes.

Overall, this study aims to provide greater flexibility in timing transfer by providing participants with vaginal pessaries of P4 to be used before FET and, subsequently, confirming the absence of elevated endogenous P4 on the day of P4 supplementation start and confirming the presence of a corpus luteum on an ultrasound scan. It is hypothesized that the potential advantages of this P4mNFET protocol, over triggering and manipulating ovulation, may include the increased flexibility in the timing of commencing P4 without the requirement of a large follicle, the elimination of the importance of pinpointing the exact timing of ovulation, and the potential cost-saving to the patient and clinic as a result of these components. It is anticipated that the outcomes of this pilot cohort study may inform the planning and development of a subsequent noninferiority RCT to further reinforce the utility of such a protocol.

## Methods

### Study Type

The proposed study will adopt a pilot cohort methodology consisting of 12 weeks of intervention and follow-up monitoring of participants for primary and secondary outcomes. Secondary outcomes will be compared with retrospective data from the tNFET control group.

### Participants

The study population will consist of 20 women undertaking FET cycles at the Public Fertility Care of The Royal Women’s Hospital (RWH), Melbourne, Australia. The recruitment process will commence at this location, whereby clinicians and nursing teams will be invited to screen the patients they interact with for eligibility for the study. These staff members will be trained on appropriate screening according to the study protocol and will be delegated by the principal investigator. Eligible patients will then be approached for study by team members who are not directly involved in potential participants’ clinical care and, therefore, will not have had any clinical interactions with the participant. All patients will be provided with a patient informed consent form (Multimedia Appendix 1) to ensure they are familiar with the protocol requirements and understand their rights as participants. Additionally, they will be provided with a patient information document created by the research team (Multimedia Appendix 2) to assist with patient education surrounding the use of the P4 pessary during the study.

Inclusion criteria consist of women with regular cycles defined as 21-35 days, women younger than 40 years at the start of a cycle, and women whose BMI ranges from 18 to 35, inclusively.

The exclusion criteria include anovulatory women, women who are 40 years or older at the start of the cycle, and women who have preexisting contraindications to exogenous P4 supplementation, such as those with liver disease or thromboembolic disease. The exclusion criteria will also include the use of additional LPS (eg, subcutaneous), women with uterine pathology, including congenital malformations of the female reproductive tract, endometrial polyps, intrauterine adhesions, adenomyosis, and leiomyoma. Regarding the retrospective element of the study, patients for whom inclusion criteria information is lacking will not be included in the study.

The control group will consist of retrospective data from 20 women, matched against inclusion and exclusion criteria, within the Public Fertility Services of the RWH data bank. These controls would have undergone tNFET at the service provider within the preceding 12 months of the study start date.

All participant data will be stored securely in the database of the RWH Reproductive Services Unit (RSU), ensuring the security of patients’ confidential information. Furthermore, on completion of the study, all patient information will be securely stored within the hospital server with restricted access for a minimum of 15 years, with custodial responsibilities given to the principal investigator.

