### Control: tNFET Protocol

The control group will consist of patients, matched to the inclusion and exclusion criteria, who would have undergone tNFET at the RWH RSU. Patients undertake an ultrasound on days 10-12 of their cycle for those with a 28-day cycle. Upon detection of a dominant follicle of 18 mm or more and an endometrial thickness of 7 mm or more, serum LH and P4 are taken. An LH surge is defined as >25 IU/L in the context of P4 <5 nmol/L. Ovulation is defined as a P4 >5 nmol/L. LPS, in the form of a vaginal ORIPRO 200 mg pessary (Orion Laboratories Pty Ltd T/A Perrigo, Australia), is commenced on day 1 post ovulation, and embryo transfer is carried out 6 days post LH surge.

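### The controls are called matched but are only restricted to the same eligibility criteria, and 20 are taken from completed cycles with no stated rule for which 20

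*Protocol article*

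**What the plan says.** The abstract's Methods paragraph tells the reader: "These women will be matched to a control group who have undergone the tNFET protocol within the preceding 12 months of the study start date". The body of the article then says what this means. Under Participants: "The control group will consist of retrospective data from 20 women, matched against inclusion and exclusion criteria". The section headed Control: tNFET Protocol gives the same definition again: "The control group will consist of patients, matched to the inclusion and exclusion criteria, who would have undergone tNFET at the RWH RSU". No matching variable is named in any of the three places.

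The window is given under Participants: "These controls would have undergone tNFET at the service provider within the preceding 12 months of the study start date". The intervention group is the same size: "The study population will consist of 20 women undertaking FET cycles". The only further filter on the controls is that "patients for whom inclusion criteria information is lacking will not be included in the study".

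Study Type says that the controls are used for the secondary outcomes, which Outcome Measures lists as clinic visits, biochemical pregnancy and clinical pregnancy. Statistical Analysis and Sample Size adds a multivariate analysis if key baseline variables vary significantly between the groups. It does not name those variables.

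**The concern.** Matching normally means that each study participant, or the study group as a whole, is paired or balanced with controls on named prognostic variables. Here both groups merely pass the same entry filter. That filter is wide: "women younger than 40 years at the start of a cycle, and women whose BMI ranges from 18 to 35, inclusively", with regular cycles of 21 to 35 days. Two groups could sit at opposite ends of the age range, or differ in embryo stage or number of previous transfers, and still satisfy this description. A reader of the abstract would credit the comparison with protection it lacks.

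The second issue is how 20 women are reached. The controls had their transfers before the study began, so most or all of their pregnancy results will exist when records are pulled. This is inferred from the retrospective source; the article does not say it in words. If more than 20 qualify, someone must choose, and nothing in the text makes that choice consecutive, random or blind to outcome.

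At stake are the pregnancy and visit comparisons. The Discussion looks forward to no impact on pregnancy outcomes (Overview) and to outcomes comparable with established methods (Implications), and the study is meant to inform a noninferiority RCT.

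**Working it through.** **The plan's own figure.** The article gives no derivation for 20 controls, so there is no calculation to reproduce.

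**What the matching equalises.** Set side by side, the abstract matches *women to a control group*, while the two body sections match *controls to criteria*. Only the second is defined, and it adds nothing to eligibility.

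**Inputs.** 20 study women and 20 controls (Participants). The eligible pool M and the pregnancy rate p are not in the article. I assume M from 20 to 200 and p = 40%.

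**Room for choice if outcomes are visible.** With K = pM pregnancies in the pool, the number of pregnancies among 20 chosen controls can lie between max(0, 20 − (M − K)) and min(20, K).

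| Pool M | Pregnant K | Lowest control rate | Highest control rate |
|---|---|---|---|
| 20 | 8 | 40% | 40% |
| 30 | 12 | 2/20 = 10% | 12/20 = 60% |
| 40 | 16 | 0% | 16/20 = 80% |
| 60 | 24 | 0% | 100% |

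These are outer limits, not predictions. They show that the plan as worded places no bound on the control rate once the pool is moderately larger than 20, and that the problem vanishes if exactly 20 qualify.

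**Precision lost by stopping at 20.** For a difference in proportions with a common rate p, SE = √[p(1 − p)(1/20 + 1/m)] with m controls. Relative to 20 v 20, the ratio is √[(1/20 + 1/m)/(2/20)], which does not depend on p. For m = 60: √(0.0667/0.10) = 0.816.

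| Controls m | SE ratio | 95% half-width at p = 40% |
|---|---|---|
| 20 | 1.000 | 30.4 points |
| 40 | 0.866 | 26.3 points |
| 60 | 0.816 | 24.8 points |
| 100 | 0.775 | 23.5 points |
| 200 | 0.742 | 22.5 points |

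**Does the conditional adjustment rescue the comparison?** If *significant* means a two-sided 5% test, a true imbalance of half a standard deviation in a baseline variable is detected with power 35% at 20 per group. It would therefore go unadjusted about 65% of the time. Adjustment for baseline variables also cannot undo a choice of controls made on outcome.

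**The case against.** Several points on the other side are fair.

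- **Limited reach.** The primary outcome, the corpus luteum on the day of transfer, is not compared with controls, and Implications ties progression to an RCT to that outcome. This stands, and it caps the importance of the point.
- **Adjustment is planned.** It is, and it is a partial safeguard against baseline imbalance. It is conditional, names no covariates and has 40 women to work with.
- **The article condenses a fuller protocol.** A sampling rule may exist there, so its absence here does not prove that there is none. But the article does define its matching, twice, and that definition does not support the abstract.
- **The gain is modest.** At 60 controls the half-width is still about 25 points, too wide to settle pregnancy rates. True; the main benefit of taking everyone is that it removes the choice.

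A reader might also infer more than the text supports:

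- *That control data are certainly being discarded.* The number of eligible cycles is not given, so this is conditional.
- *That controls with no record of uterine pathology are kept.* The missing-information sentence names inclusion criteria only, but both control descriptions require the exclusion criteria to be met as well. The wording is ambiguous; no such control is said to be retained.
- *That the same women will appear in both groups.* Nothing prevents it, and the planned t and Mann-Whitney tests assume independent groups, but no figure for repeat transfers is given.
- *That random sampling error measures the bias.* Drawing 20 at random from an assumed 60 with 35% pregnant has SD √(20 × 0.35 × 0.65 × 40/59) = 1.76 women, so about ±17 points (1.96 × 1.76/20). That is chance variation, not selection bias.

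**Conclusion.** The point holds in two parts. First, without any assumption, *matched* is a misleading word for an eligibility filter, in the abstract and in both body sections. Second, fixing 20 controls from a bank of completed cycles without a selection rule leaves room for outcome-aware choice and wastes data, provided that more than 20 women are eligible. On assumed pools of 40 to 200, using all controls would bring the standard error to about 0.87 to 0.74 of the 20 v 20 value (0.82 at 60). With exactly 20 eligible there is no leeway and no gain, and only the labelling fault remains.

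The consequence is confined to clinic visits and the two pregnancy rates. The article's Anticipated Challenges and Limitations sections admit problems of data accuracy and data entry in the controls, and the lesser rigour of a cohort in general. They do not mention selection or confounding of the controls. This should be changed, but it does not undermine the primary outcome.

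**What to change.** 1. Replace the 20 matched women with every woman who had an eligible tNFET cycle at the service in the 12 months before study start. Use one cycle per woman, chosen by a fixed outcome-blind rule, for example the first in the window.
2. If extraction must be capped, take the most recent consecutive eligible cycles, or match on named factors such as age and embryo stage. Either should be done without sight of the outcome.
3. Unless true matching factors are used, delete *matched* in all three places and describe a historical, eligibility-restricted control. Add selection and confounding of the controls to Limitations.
4. Apply the missing-information rule to exclusion as well as inclusion criteria.
5. Do not drop controls who later join the study arm. They would mostly be women whose control transfer failed, so dropping them raises the control rate: with an assumed 21 pregnancies in 60, removing 5 failures gives 21/55 = 38% and removing 10 gives 21/50 = 42%, against 35%. Keep them, report the overlap and run a sensitivity analysis.

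The cost is some extra record extraction from an existing data bank and a few sentences of text. No new participants are needed.

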### Statistical Analysis and Sample Size

Given the qualitative and binary nature of the primary outcome, no statistical testing is proposed for this. Secondary outcomes will undergo *t* tests and Mann-Whitney *U* tests for data that are normally and not normally distributed, respectively. Should there be significant variation in the key baseline variables between the study and the control group, a multivariate analysis will be performed.

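### Controls are matched on eligibility alone, so transfer history can differ between the groups, a woman can be in both, and the unstated choice of control cycle can itself shift the pregnancy comparison

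*Protocol article*

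**What the plan says.** All references are to the protocol article.

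- **Study group (Participants).** "The study population will consist of 20 women undertaking FET cycles at the Public Fertility Care of The Royal Women’s Hospital".
- **Control group (Participants).** "The control group will consist of retrospective data from 20 women, matched against inclusion and exclusion criteria". On timing: "These controls would have undergone tNFET at the service provider within the preceding 12 months of the study start date".
- **Eligibility (Participants).** The inclusion list is "women with regular cycles defined as 21-35 days, women younger than 40 years at the start of a cycle, and women whose BMI ranges", followed by the BMI limits. The exclusions cover anovulation, age, contraindications to progesterone, additional luteal support and uterine pathology. Neither list mentions earlier transfers or earlier service as a control.
- **Timing (Results).** The study began in September 2024 and was planned to take 9 months. The control window therefore runs from about September 2023 and ends where recruitment begins.
- **Use of the controls (Study Type).** "Secondary outcomes will be compared with retrospective data from the tNFET control group". These outcomes are clinic visits, biochemical pregnancy and clinical pregnancy.
- **Analysis (Statistical Analysis and Sample Size).** "Secondary outcomes will undergo *t* tests and Mann-Whitney *U* tests". A multivariate analysis follows only if unnamed key baseline variables vary significantly between the groups. The primary outcome is not tested.
- **Acknowledged weaknesses (Anticipated Challenges; Limitations).** For the control group, only the accuracy and entry of retrospective data are named.

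**The concern.** Matching on the inclusion and exclusion criteria means only that each control would have been eligible. It does not make the groups alike in transfer history, which plausibly predicts the next result.

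The two windows are linked selectively. A woman with an ongoing pregnancy from a control-window tNFET cannot enrol, whereas one whose transfer failed, or who lost the pregnancy, can. A woman who appears in both groups will thus mostly bring a failed cycle to the control side, and the two-sample tests assume that she does not exist.

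The article says 20 women, which implies one cycle each, but a woman with several tNFET cycles in the window offers a choice. A woman usually stops after a success, so her last cycle in the window is more likely to be a success than her first. How the cycle is picked can therefore create a difference between the groups without any treatment effect. The study is meant to inform a noninferiority trial of the same two protocols, where an artefact in the pregnancy rates could mislead planning.

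**Working it through.** **The plan's own figures.** There is none to reproduce: the article gives 20 and 20 women, with no pregnancy rate, pool size or share of returning patients. Everything below rests on assumed values.

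**1. How many women could be in both groups?** Let *s* be the share of the 20 recruits with a tNFET cycle in the control window and *N* the number of eligible control women, with 20 controls drawn at random.

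Expected overlap = 20 × *s* × 20/*N*; chance of at least one = 1 − (1 − 20/*N*)^(20*s*).

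| *N* (assumed) | *s* = 20% | *s* = 50% |
|---|---|---|
| 40 | 2.0 women; 94% | 5.0 women; >99% |
| 100 | 0.8; 59% | 2.0; 89% |
| 600 | 0.13; 13% | 0.33; 29% |

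For example, with *N* = 100 and *s* = 20%: 20 × 0.2 × 0.2 = 0.8, and 1 − 0.8⁴ = 0.59.

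**2. Does transfer history differ, and does the choice of cycle matter?** A clinic in steady state was simulated. Assumptions: mean pregnancy rate 35% per transfer; 50% or 80% return after a failure; 1 to 5 months between transfers; between-woman variation either none or a Beta distribution with concentration 4 or 10; no return after a pregnancy; control window months −12 to 0; study window months 0 to 9; each study woman enters at her first transfer in the study window; no treatment effect. Ranges are over the six combinations.

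| Control cycle used | Controls with a prior failure | Control pregnancy rate | Control minus study rate |
|---|---|---|---|
| First in window | 11–26% | 32–35% | under 1 point |
| Every cycle counted | 33–58% | 28–35% | about 0 to −3 points |
| One of her cycles at random | 22–42% | 38–45% | about +4 to +10 points |
| Last in window | 33–55% | 43–57% | about +9 to +22 points |
| First in window, later enrollees removed | not tabulated | 39–45% | about +4 to +12 points |

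In the study group, 14–32% had a prior failure and the pregnancy rate was 31–35%. The last row is an extreme: every eligible returner is recruited and removed from the controls.

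**3. Hand check on transfer history.** Suppose first transfers succeed at 40% and transfers after a failure at 25% (assumed). A group with a share *q* of prior failures has rate 0.40 − 0.15*q*, so study minus control = 0.15 × (*q* control − *q* study). With first-in-window controls, the study share is 3 to 6 points higher, so the study rate is lower by 0.15 × 3 = 0.5 to 0.15 × 6 = 0.9 points. With every cycle counted, the control share is 19 to 26 points higher, so the study rate is higher by 0.15 × 19 = 2.9 to 0.15 × 26 = 3.9 points. The sign changes with the selection rule.

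**4. Hand check on removing controls who later enrol.** Take 60 eligible tNFET women, 21 pregnant (assumed): 21/60 = 35%. If 5, 10 or 15 women with failed cycles enrol and are dropped, the control rate becomes 21/55 = 38%, 21/50 = 42% or 21/45 = 47%. The last case needs 15 of the 20 recruits to come from that group.

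**5. Does matching on transfer order help?** Given the transfer order, both groups have been through the same number of failures. In the simulation, taking control cycles of the participants' orders without regard to outcome, and keeping controls who later enrolled, brought the two rates to within about half a point.

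**The case against.** A reader might infer that the study group is necessarily enriched for earlier failures, so that the comparison is biased against P4mNFET by construction. The documents do not support this. Women at their first transfer can be recruited, and controls may themselves have returned after an earlier failure. The article does not say how many recruits are returners. In the simulation, the prior-failure gap is small with first-in-window controls and reverses when every control cycle is counted.

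Three further objections carry weight.

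- **Consequence.** Only secondary outcomes are compared with controls, and the Implications section ties the step to a randomized trial to the corpus luteum finding. At 20 per group and a 35% rate, the 95% margin on a difference is about 1.96 × √(2 × 0.35 × 0.65/20) = 30 points, and power for 35% against 25% is about 10%. A shift of a few points would not be visible. This limits the importance of the point, but imprecision does not remove a systematic error from an estimate that may be carried forward.
- **Condensed article.** The full protocol, not shown, may contain an overlap rule or name further matching variables. That is possible. The article does, however, state the control source, the window and the basis of matching, and that scheme is what permits the problem.
- **Adjustment.** Prior transfers could be among the unnamed key variables. But adjustment depends on significant variation, which groups of 20 will often fail to show, and it would not undo selection of cycles by outcome.

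No passage proposes removing overlapping women from the controls. That figure is a warning about an obvious repair, not a measure of the stated plan.

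**Conclusion.** The concern holds in limited form. As described, the control scheme allows unequal transfer history and allows a woman to be in both groups, while the planned tests assume independent groups. That follows from the text.

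The size and direction of any bias do not. Under the assumed clinic parameters the artefact in the pregnancy rate runs from under 1 point (first in-window cycle) to 10 points or more (last in-window cycle, or, where most women return after a failure, removal of controls who later enrol). Counting every control cycle moves it the other way. Expected overlap runs from about 0.1 to 5 women, depending on a pool size and a share of returners that the article does not give.

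The pregnancy comparisons are the ones mainly affected. Clinic visits are touched chiefly through the lack of independence, and the primary outcome not at all. The change is worth making because the choice of control cycle can matter more than chance differences in transfer history, and it costs little to fix in advance.

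**What to change.** Replace matching on eligibility alone with a stated selection rule:

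1. Record transfer order, or the number of previous failed transfers, for every participant and candidate control. Match control cycles to participants on it.
2. Use one cycle per control woman, chosen by a rule fixed in advance and blind to outcome. For example, draw at random among women with an eligible cycle of the required order. Do not use the last cycle in the window, and do not draw at random among one woman's own cycles, which also favours successes.
3. Do not remove a control because she later enrolled.
4. Report how many women are in both groups.
5. Add a sensitivity analysis of the pregnancy outcomes limited to first transfers in both groups. No woman can then be in both, so the independence assumption is met in that respect.

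If the full protocol already has such rules, it is enough to state them with the results.

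The cost is one item from clinic records, a short paragraph on control selection and one extra analysis. The downside is a smaller eligible control pool and low precision in the first-transfer subset, which will be smaller than 20 per group if any participant is a returner.
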